### Sample size

We propose to enroll 216 participants, 144 in the Tai Chi group and 72 in the aerobic exercise group. Power analyses are based on hypothesized changes in FIQR total scores. We used the outcomes of two previous randomized trials to formulate expected effects. Both studies used education controls. The first study by Rooks and colleagues [73] compared the effects of a 16-week aerobic and flexibility exercise program with an education group among 101 participants with fibromyalgia. They found that the aerobic and flexibility exercise group had a 7.9-point mean improvement in the Fibromyalgia Impact Questionnaire (FIQ), yielding an effect size of 0.62. The second study, our pilot trial of 66 participants with fibromyalgia, compared 12-weeks of Tai Chi with a wellness education control [40]. We found an 18.4-point mean improvement in the FIQ score in the Tai Chi group, yielding an effect size of 1.04. We hypothesize that patients receiving Tai Chi will improve more than those receiving aerobic exercise. Using a two-sided hypothesis test at a 0.05 significance level with an allocation ratio of 2:1, a total sample size of 216 (144 in the Tai Chi group, 72 in the aerobic exercise group) would give about 80% power to detect a conservative effect size of 0.4.

We also seek to elucidate how four different schedules of dose and frequency might modify the impact of Tai Chi. With 36 individuals per group, we would have 80% power to detect an effect size of 0.67 between two of these groups with a two-sided 0.05 level test. We will also gain power from the additional individuals tested in the other groups as well as from the blocking by instructor.

### Data analysis

The primary outcome (change in FIQR between baseline and 24 weeks) will be compared between the five treatment groups using intention-to-treat with a two-sided significance level set at 5%. Participants who withdraw will be treated as having no change from baseline at all times after dropping out. The primary analysis will be a mixed model analysis of variance adjusting for the random blocking factor of instructor. If any characteristics differ substantially at baseline, we will adjust for them in a mixed-model regression analysis. To protect against multiple comparisons, we will only evaluate between-group differences if the overall effect of treatment is significant. If so, we will examine the following contrasts: 1) Tai Chi (four groups) versus aerobic exercise; 2) Tai Chi (12 weeks) versus Tai Chi (24 weeks); 3) Tai Chi once per week versus Tai Chi twice per week; and 4) interaction of number of treatments per week and length of treatment. We will also examine whether treatment effects differ by instructor.

Secondary analyses will examine change in FIQR from baseline to 12 and 52 weeks as well as secondary outcomes for change at 12, 24, and 52 weeks. Continuous outcomes will be compared by linear regression, and discrete outcomes by logistic regression. All analyses will follow the template for the primary outcome in the previous paragraph, using mixed models with adjustment for instructor examining treatment duration and frequency. If the instructor effect is not significant, we will present results summarized across instructors. All regression models will be assessed by regression diagnostics for adherence to model assumptions. To explore potential psychological and psychosocial mediators (for example, depression, self-efficacy, social support) that may be useful in future research, we will examine treatment interactions with a list of pre-defined moderators. To control for multiple testing, we will perform these tests at a conservative significance level adjusted for the number of moderators tested. In addition, we will also perform longitudinal analyses in which measurements at baseline, 12, 24, and 52 weeks are jointly analyzed using appropriate mixed models including time as a categorical fixed factor with random intercepts and first-order autocorrelation of the errors. Similar mixed models will be used to examine the weekly FIQR measurements taken in the intervention period. We will also check for potential confounding and interaction between time, treatment, instructor and other significant covariates. In addition to intent-to-treat analyses in which dropouts are treated as having no effect, we will also perform secondary analyses using multiple imputation and checks of the mechanism by which participants drop out to determine whether ignorable or nonignorable missing data methods are required [74,75]. If nonignorable methods are needed, we will explore both selection and pattern-mixture types [74,75].

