### Aerobic exercise training

Participants randomized to aerobic exercise receive a closely supervised, group-format cardiovascular (aerobic) exercise program located on our Tufts Campus. The program is consistent with the current recommended guidelines of moderate intensity exercises for fibromyalgia [8,9,21].

In the fibromyalgia population, lower levels of cardiovascular fitness and lower thresholds for post-exercise muscle pain and fatigue are reported [2,3]. Compliance may be compromised due to training that is too intense or to a lack of supervision. Therefore, our program is individually tailored to each participant, closely supervised, introduced in a progressive manner, and gradually increased in volume and intensity to achieve the target of moderate-intensity exercise. The senior scientist in exercise physiology ([name]) has over 20 years experience in conducting exercise trials, oversees the program and runs training sessions for the exercise instructors at study initiation and throughout the trial. The experienced instructors perform the exercise regimen. Each session lasts 60 minutes, twice a week, for 24 weeks. We instruct participants to walk daily on their own, gradually increasing their time until they reach 30 minutes a day. We also provide the participants with printed materials on fibromyalgia and the aerobic exercise program, including aerobic exercise principles, practicing techniques, and safety precautions for participants with fibromyalgia.

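### The primary analysis sets every withdrawal to zero change in FIQR, so with two active arms the treatment contrast is mixed with any difference in retention

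*Protocol article*

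**What the plan says.** The Data analysis section of the protocol article compares the change in FIQR from baseline to 24 weeks across five groups, "using intention-to-treat with a two-sided significance level set at 5" per cent. It then fixes how withdrawals enter that comparison: "Participants who withdraw will be treated as having no change from baseline at all times after dropping out". The four contrasts (Tai Chi v aerobic, duration, frequency and their interaction) are examined only if the overall treatment effect is significant.

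Multiple imputation and longitudinal mixed models appear later in the same section, as secondary analyses. Selection and pattern-mixture models follow only if needed, after "checks of the mechanism by which participants drop out to determine whether ignorable or nonignorable missing data methods are required".

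The Sample size section expects improvement with either treatment. It cites a "7.9-point mean improvement in the Fibromyalgia Impact Questionnaire (FIQ), yielding an effect size of 0.62" for an aerobic and flexibility programme, and 18.4 points (effect size 1.04) for Tai Chi. It states that "a total sample size of 216 (144 in the Tai Chi group, 72 in the aerobic exercise group) would give about 80% power" for an effect size of 0.4. It gives no dropout rate and no attrition allowance. The Primary outcome section says that FIQR is also collected weekly during the intervention period in all groups.

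**The concern.** Against an inert control, setting withdrawals to zero change usually pulls the treated arm towards the control. Here both arms are active. Every withdrawal removes an expected improvement from the arm it occurs in, so the contrast estimates the treatment difference combined with the retention difference. The direction is not fixed: the rule favours whichever arm keeps more of its participants.

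The duration and frequency contrasts are affected in the same way if retention differs between Tai Chi schedules. The trial's main conclusion, and its answers on schedule, could therefore be created, enlarged or hidden by retention alone.

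**Working it through.** **Inputs from the protocol article.** Group sizes are 144 and 72; the test is two-sided at 0.05; the planned effect is 0.4 SD; the cited improvements are 7.9 points (0.62 SD) and 18.4 points (1.04 SD).

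**Assumptions.**
- SD = 18.4/1.04 = 17.7, reading the effect size as mean improvement over SD. The aerobic figures imply 7.9/0.62 = 12.7.
- Dropout is 10% to 30% per arm and random within arm.
- The 15-point improvement is a value chosen between the two cited ones.
- The instructor effect is not modelled.

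**The plan's own figures.** SE = √(1/144 + 1/72) = 0.1443 SD and 0.4/0.1443 = 2.77, so power = Φ(2.77 − 1.96) = 79% (78.8% with the noncentral t). For 36 v 36 and an effect of 0.67, the noncentral t gives 80%. Both stated figures reproduce, with no dropout and no overall-test gate.

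**Effect of the rule.** With mean improvement m (in SD) and dropout d:
- arm mean = (1 − d)m
- arm variance = (1 − d)(1 + d·m²), over the full randomised n.

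**Equal true improvement, dropout 10% Tai Chi v 30% aerobic.** The false difference is (0.90 − 0.70) × improvement.

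Worked example for 15 points:
- m = 15/17.7 = 0.847, and the false difference is 0.20 × 15 = 3.0 points = 0.169 SD.
- The variances are 0.965 and 0.851, pooled 0.927; SE = √(0.927 × (1/144 + 1/72)) = 0.139.
- z = 0.169/0.139 = 1.22, and the rejection rate is Φ(1.22 − 1.96) = 23%.

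The last two columns come from simulating the five-group F test followed by the contrast.

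| True improvement, both arms | False difference | Contrast alone rejects | Overall test rejects | Contrast rejects after overall test |
|---|---|---|---|---|
| 7.9 points | 1.6 points | about 9–10% | about 8% | about 4% |
| 15 points | 3.0 points | about 23% | about 14% | about 10% |
| 18.4 points | 3.7 points | about 31% | about 18% | about 15% |

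With equal 20% dropout, the contrast alone and the overall test both stay at 5%, and the contrast after the overall test rejects about 1.5% of the time. With milder imbalance (15% v 25%) and 15 points, the false difference is 0.10 × 15 = 1.5 points; the contrast rejects about 9% alone and about 3.4% after the overall test. If the 7.9-point improvement is scaled by its own SD (m = 0.62), 10% v 30% gives 14–16% alone, 10% for the overall test and 6% after it. Swapping the dropout rates reverses the sign.

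**True effect 0.4 SD (Tai Chi 1.02, aerobic 0.62); power of the contrast alone.**
- 10% v 30%: 0.90 × 1.02 − 0.70 × 0.62 = 0.918 − 0.434 = 0.48; power about 94–95%.
- 30% v 10%: 0.70 × 1.02 − 0.90 × 0.62 = 0.714 − 0.558 = 0.16; power about 20%.
- 20% v 20%: 0.80 × 0.40 = 0.32; power about 63–66%, depending on how the variance is pooled. Observed data only, with n reduced by 20%, give about 69%.

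**The case against.** Several stronger readings are tempting, and the document does not support them.

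- **Ungated error rates.** The 23% and 31% describe the contrast on its own. The plan tests it only after a significant overall test, which brings the rates down to about 10% and 15%. The gate limits the problem but does not remove it, and the gate's own error rate rises above 5%.
- **Standard error.** A reader might infer that imputed zeros shrink the standard error and so inflate false positives. With equal dropout the error rate stays at 5%, because the estimate shrinks too and the standard error matches the variability of the zero-filled data. The inflation comes from bias under unequal dropout.
- **Expected aerobic dropout.** The Aerobic exercise training section says "Compliance may be compromised due to training that is too intense or to a lack of supervision", but goes on to describe tailoring and close supervision as the response. The Background reports that most aerobic studies met their adherence goals. The document does not predict greater loss in that arm.
- **Longer exposure in the 24-week groups.** All groups share the week-24 endpoint and are followed to week 52. Supervised class time differs; time at risk of withdrawal before the endpoint does not.
- **Discarded weekly scores.** Scores before withdrawal stand and enter secondary mixed models. They are only unused in filling the primary endpoint.
- **A rule presented as conservative.** The protocol never calls it that; the word describes the effect size of 0.4. For superiority of Tai Chi the rule is in fact conservative when dropout is equal or higher in Tai Chi.

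It is also fair that no dropout rate is documented, that the size depends on assumed values, that better methods are already planned, and that most of the power loss under equal dropout is attrition itself. What stands is that those methods do not determine the primary result, and that the direction of the bias cannot be known in advance.

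**Conclusion.** The concern holds for the primary estimate. Zero-change imputation biases every between-group contrast by the retention difference times the improvement lost. At 10% v 30% dropout, the bias on Tai Chi v aerobic is 1.6 to 3.7 points over the cited range of improvements, with a false-positive rate after the overall test of about 4% to 15% instead of about 1.5%. At the low end of that range the gated rate stays below 5%. A true effect of 0.4 SD may be estimated anywhere from 0.16 to 0.48 as the 10%/30% imbalance changes direction. These sizes rest on SD 17.7, random dropout and assumed rates; with equal dropout there is dilution but no false difference.

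Two smaller points follow. The stated power of about 80% holds only with no attrition. And making nonignorable methods conditional on a check of the dropout mechanism cannot work as described, because observed data alone cannot show whether missingness is ignorable.

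**What to change.** - Make the planned likelihood-based mixed model, or multiple imputation using the weekly, 12-week and 24-week FIQR, the primary analysis.
- State that week-24 FIQR is used for participants who stopped classes but were assessed. The present wording refers to withdrawal and does not settle this case.
- Keep zero change as a sensitivity analysis.
- Run a pattern-mixture or delta-adjusted analysis in every case, not only after a mechanism check.
- Restate power with an assumed attrition rate. On observed data alone, 20% in each arm gives about 69% for the effect of 0.4.

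The cost is a change of analysis wording. The data are already collected and the main methods already planned, so they swap roles. The downside is that the primary result then rests on missing at random, which is why the nonignorable sensitivity analysis should be unconditional.

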### Randomization

Randomization occurs after the baseline evaluation. The study statistician ([name]) randomizes assignments using a sequence randomly generated in the R statistical package [41]. These assignments are then sent to a study staff member other than the study coordinator or principal investigator, who puts them into sealed, opaque envelopes with date and signature labels placed over the seals of the envelopes. The study coordinator then contacts eligible participants by phone, and confirms that each one still wishes to participate in the study and is able to make the time commitment to either intervention group. Upon confirmation, the study coordinator opens the consecutive randomization envelope and informs the individuals of their group assignments. The study coordinator also informs the participants of the schedule for their training sessions (including date and time). Randomization envelopes are not opened unless a participant meets eligibility criteria, completes the informed consent, and undergoes a baseline assessment.

The study is conducted in six different cycles. Each cycle consists of an aerobic exercise intervention group and two of the four Tai Chi intervention groups. The Tai Chi intervention groups are rotated through the six cycles so that each one (12 or 24 weeks of supervised Tai Chi, once or twice per week) occurs three times over the course of the study. We use a factorial arrangement to ensure that each of the three Tai Chi instructors conducts each of the four treatments (Tai Chi once or twice per week for each of 12 and 24 weeks) once during the trial. This arrangement is subject to the constraints that two sessions are given in each of the six cycles, that each instructor teaches twice in each of the first three and last three cycles, that no instructor teaches more than once in any single cycle and that each treatment is given at least once and no more than twice in the first three sessions and in the last three sessions. Each instructor is therefore idle for two of the six sessions. The design for each of the four treatments (A, B, C and D) is listed in Table 3. The instructors are randomly assigned to be I, II or III, and each of the four treatments is randomly assigned to be A, B, C or D. Each resulting group consists of 12 patients, for a total of 36 patients participating in each cycle and 216 over the course of the six cycles comprising the study.

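### The primary model has no term for the 18 classes of 12, its only random factor is laid out for Tai Chi alone, and both power figures assume independent patients

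*Protocol article*

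**What the plan says.** The Randomization section and Table 3 set out six cycles, each with one aerobic class and two Tai Chi classes: "Each resulting group consists of 12 patients, for a total of 36 patients participating in each cycle". That makes 18 classes. Each of the three Tai Chi instructors teaches each of the four schedules once. The Study intervention section adds that every class is fully assembled before treatment starts.

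The aerobic arm has instructors too: "The experienced instructors perform the exercise regimen". Their number, their allocation to classes and their place in the blocking factor are not stated, and Table 3 does not include them.

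The Data analysis section fixes the model: "The primary analysis will be a mixed model analysis of variance adjusting for the random blocking factor of instructor". It names no class or cycle term. Contrasts are examined only if the overall five-group test is significant, and a separate look at instructor differences in the treatment effect is planned.

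The Sample size section says: "We propose to enroll 216 participants, 144 in the Tai Chi group and 72 in the aerobic exercise group". This "would give about 80% power to detect a conservative effect size of 0.4". For the schedules it says: "With 36 individuals per group, we would have 80% power to detect an effect size of 0.67 between two of these groups". It gives no ICC or design effect, and counts instructor blocking only as a benefit: "We will also gain power from the additional individuals tested in the other groups as well as from the blocking by instructor".

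**The concern.** People in one class share an instructor, peers and dates for 12 or 24 weeks, so their outcomes may be correlated. A random instructor intercept gives an instructor's four classes one common shift. It leaves the differences between those classes in the residual, where they are treated as person-level noise. In the aerobic arm it is not clear what the factor represents at all.

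The overall treatment test is at stake first, because it is the plan's only protection against multiple comparisons. The schedule contrasts and the main comparison follow. The stated power also describes an individually delivered trial rather than a class-delivered one.

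There is a related identification problem. Each instructor-by-schedule cell is a single class, so a difference between instructors in the treatment effect cannot be told apart from a class effect. The Discussion nevertheless uses instructor differences to judge how widely the benefit generalises.

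**Working it through.** **Inputs from the article.** 144 versus 72 participants, two-sided 5%, effect size 0.4; 36 versus 36, effect size 0.67; class size 12; 12 + 6 = 18 classes. **Assumed:** class ICC of 0.01 to 0.10, because the article gives none. Total SD is set to 1.

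**Step 1: reproduce the stated power under independence.**
- Tai Chi versus aerobic: SE = √(1/144 + 1/72) = 0.1443; power = Φ(0.4/0.1443 − 1.96) = 79.1%.
- Two schedules: SE = √(2/36) = 0.2357; power = Φ(0.67/0.2357 − 1.96) = 81.1%.

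Both agree with the stated 80%, so both figures assume an ICC of zero.

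**Step 2: allow for class-specific correlation.** Design effect DEFF = 1 + (12 − 1) × ICC; SE is multiplied by √DEFF.

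| Class ICC | DEFF | SE (144 v 72) | Power at 0.4 | Power at 0.4, t on 18 − 2 = 16 df | Power at 0.67, 36 v 36 |
|---|---|---|---|---|---|
| 0 | 1.00 | 0.144 | 79% | 74% | 81% |
| 0.01 | 1.11 | 0.152 | 75% | 70% | 77% |
| 0.02 | 1.22 | 0.159 | 71% | 65% | 73% |
| 0.05 | 1.55 | 0.180 | 60% | 55% | 63% |
| 0.10 | 2.10 | 0.209 | 48% | 44% | 50% |

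The last column is a large-sample figure. Only six classes inform a comparison of two schedules, so it is optimistic. For Tai Chi versus aerobic, the effect detectable with 80% power rises from 0.40 at ICC 0 to 0.45 / 0.50 / 0.59 at ICC 0.02 / 0.05 / 0.10.

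**Step 3: type I error of an instructor-only model.** Data were simulated with no treatment effect, using the article's layout and class-specific correlation. Instructor was coded in two ways: random for Tai Chi only (REML, Wald test), or as a fixed block with pooled residual.

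| Test | Coding | ICC 0.02 | ICC 0.05 | ICC 0.10 |
|---|---|---|---|---|
| Overall, 4 df | random | 8.5% | 19.4% | 34.3% |
| Overall, 4 df | fixed | about 10% | about 19% | about 35% |
| Two-versus-two schedule contrast | random | 7.0% | 12.3% | 18.5% |
| Two-versus-two schedule contrast | fixed | 7.8% | 12.0% | 18.5% |
| Tai Chi versus aerobic | random | 5.7% | 9.2% | 13.3% |
| Tai Chi versus aerobic | fixed | 7.5% | 11.6% | 18.0% |

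At ICC 0 all of these are near 5%.

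**Step 4: correlation that comes only from the cycle.** If all correlation is shared by the three concurrent classes of a cycle (fixed coding), Tai Chi versus aerobic rejects 4.7% / 4.5% / 4.1% of the time at the same ICCs. The comparison is made within cycles, so the shared shift cancels. The schedules fall in different cycles, and that contrast still rejects 6.9% / 9.3% / 13.4%.

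**Step 5: does a class term repair it?** With a random class intercept but large-sample Wald tests, the overall test rejects 5.1% / 9.5% / 11.5%. That is a large improvement, but not enough without small-sample degrees of freedom.

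**The case against.** Participants are randomized individually, so classes are not pre-existing clusters, and any correlation arises from shared delivery. It could be small. The article gives no ICC, and running both treatments concurrently balances seasonal and other cycle effects in the main comparison. A journal article may also leave the coding of a random factor to a fuller document. All of this is fair, and it makes the size of the problem conditional. It does not remove the point, because the article commits itself to a named random factor and to two power figures that hold only at an ICC of zero.

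A reader might infer more than the documents support:
- *That the aerobic arm has no instructors.* It has; what is missing is how they enter the factor.
- *That standard errors are certainly too small, for every contrast.* This depends on an unstated ICC and on its source. Step 4 shows one case in which Tai Chi versus aerobic is not inflated.
- *That the textbook formula 2Φ(−1.96/√DEFF), giving 7.6% / 11.5% / 17.6%, is the error of the planned model.* That formula has no instructor term. With random instructor for Tai Chi only, the main comparison gives 5.7% / 9.2% / 13.3%.
- *That power could collapse to about 19%.* This needs the whole aerobic arm coded as a single fourth instructor level (about 2 df, instructor ICC 0.02). The article does not state that coding, and it refers to aerobic instructors in the plural.
- *That the random instructor term should go, or that presenting pooled results after a non-significant instructor effect is an error.* A random instructor term serves the stated aim of generalising across instructors, and the pooling rule concerns presentation. Neither needs to change to repair the standard errors.

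**Conclusion.** The concern holds, conditional on positive correlation within classes. As stated, the primary model does not represent the 18 classes, and its one random factor has no defined meaning for 72 of 216 participants. The overall gating test is affected most, at about 8-10% / 19% / 34-35% instead of 5% for an assumed class ICC of 0.02 / 0.05 / 0.10. The schedule contrasts follow at about 7-8% / 12% / 18-19%. Tai Chi versus aerobic is at about 6-7% / 9-12% / 13-18%, depending on how instructor is coded, and is not inflated if the correlation is purely a cycle effect. Both stated powers are upper limits reached only at ICC 0. The ICC range is an assumption, equal class sizes of 12 are taken from the design, and no dropout is modelled. The planned examination of instructor differences cannot be separated from class effects at any ICC.

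**What to change.** 1. **Data analysis:** add a random intercept for class (18 levels) to the primary model, with cycle as a block and Kenward-Roger degrees of freedom, and use the same model for the overall test and all contrasts.
2. **Instructor:** keep an instructor term for the Tai Chi arms, and state how the aerobic arm and its instructors enter it.
3. **Instructor differences:** report the examination with the caveat that each instructor-by-schedule cell is one class.
4. **Sample size:** restate both power figures over a stated, assumed class ICC range, for example 0.01 to 0.10, and qualify the claim that instructor blocking brings a gain.

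The cost is wider intervals and fewer degrees of freedom. With five treatment means and a fixed cycle block, 18 − 5 − 5 = 8 class-level df remain, and power at effect size 0.4 would then be about 60% / 50% / 39% at ICC 0.02 / 0.05 / 0.10. Class membership follows from treatment and cycle, so no new data are needed.

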### Primary outcome

The primary outcome measure is change in the FIQR score between baseline and 24 weeks. The FIQR is a well-validated multidimensional instrument that measures participant-rated overall severity of fibromyalgia, including intensity of pain, physical function, fatigue, morning tiredness, depression, anxiety, job difficulty, and overall well-being [35]. Each item is standardized on a scale ranging from 0 to 10, with lower scores indicating more improvement or less negative impact. In addition, FIQR is also assessed weekly during the intervention period for all groups of participants as well as at the 52-week time points as secondary outcomes.

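### The primary change-score model admits baseline covariates only if they look imbalanced; fixing baseline FIQR as a covariate in advance would remove the discretion and usually gain precision

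*Protocol article*

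**What the plan says.** The Primary outcome section defines the endpoint: "The primary outcome measure is change in the FIQR score between baseline and 24 weeks". Under Data analysis, "The primary outcome (change in FIQR between baseline and 24 weeks) will be compared between the five treatment groups" at a two-sided 5% level, and the model is named: "The primary analysis will be a mixed model analysis of variance adjusting for the random blocking factor of instructor". The sentence that follows on covariates is "If any characteristics differ substantially at baseline, we will adjust for them in a mixed-model regression analysis".

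Baseline FIQR is not listed as a term in the primary model. The covariate rule does not define a substantial difference or list candidate characteristics. The same section says that the secondary analyses follow the template of the primary one. It also describes a longitudinal mixed model in which baseline is one of the repeated measurements, but as an additional analysis.

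Table 1 shows FIQR measured at baseline, and the Randomization section places randomization after the baseline evaluation. Baseline FIQR is therefore a legitimate pre-randomization covariate, already planned for every participant.

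The Sample size section is framed on change: "Power analyses are based on hypothesized changes in FIQR total scores". With 144 Tai Chi and 72 aerobic exercise participants, the design "would give about 80% power to detect a conservative effect size of 0.4".

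**The concern.** There are two separate issues.

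First, the covariates are chosen after the baseline table has been seen, against a standard that is not defined. Observed imbalance is also the wrong criterion. A covariate earns its place by predicting the outcome, and baseline FIQR can be expected to predict week-24 FIQR whether or not the groups happen to differ on it.

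Second, a change score fixes the coefficient on baseline at 1. Estimating that coefficient instead gives a residual variance that is no larger in large samples and usually smaller. The trigger would bring baseline FIQR into the model only in the minority of trials where it happens to be imbalanced, so most of the available gain would be missed.

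At stake are the precision of the Tai Chi versus aerobic exercise contrast and of the duration and frequency contrasts, and how easily the primary result can be defended once the baseline table is known.

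**Working it through.** **Inputs from the article.** 144 versus 72 participants; two-sided alpha 0.05; effect size 0.4; power about 80% (Sample size). The article does not say which SD standardizes the 0.4. Since the power analysis is framed on change, I take it as SDs of change.

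**Inputs assumed.** The correlation rho between baseline and week-24 FIQR, and k = baseline SD / week-24 SD. The article gives neither. I use rho = 0.4 to 0.7 and k = 1 down to 0.7.

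**Step 1: reproduce the stated power.** Noncentrality = 0.4 × √(144 × 72 / 216) = 0.4 × √48 = 2.771. Normal approximation: Φ(2.771 − 1.960) = 79.1%; noncentral t: 78.8%. The stated figure reproduces without any baseline adjustment.

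**Step 2: variance ratio, adjusted to change score.** With SDs s0 (baseline) and s1 (week 24):

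- Var(change) = s0² + s1² − 2·rho·s0·s1
- Var(adjusted) = s1²(1 − rho²)
- Difference = (s0 − rho·s1)², which is never negative and is zero only when k = rho
- Ratio = (1 − rho²) / (1 + k² − 2·rho·k), which reduces to (1 + rho)/2 when k = 1

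**Step 3: put in the numbers.** Power is from the noncentral t with effect size 0.4/√ratio. Equivalent N is 216/ratio.

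| k | Ratio, rho 0.4 to 0.7 | Power | Gain in equivalent participants |
|---|---|---|---|
| 1.0 | 0.70 to 0.85 | 91% to 85% | 93 to 38 |
| 0.9 | 0.77 to 0.93 | 88% to 82% | 64 to 17 |
| 0.8 | 0.84 to 0.98 | 85% to 80% | 41 to 4 |
| 0.7 | 0.90 to 1.00 | 83% to 79% | 23 to 0 |

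For example, with k = 0.8 and rho = 0.7: (1 − 0.49) / (1 + 0.64 − 1.12) = 0.51/0.52 = 0.98. At k = 1 the standard error falls by 8% to 16%.

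**Step 4: how the imbalance rule itself behaves.** This was simulated with 10,000 trials, 72 versus 144, two groups, no instructor effect, equal SDs and rho = 0.5. A substantial difference was taken as p < 0.05 on baseline FIQR, with the adjusted model replacing the unadjusted one when triggered.

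| Analysis | Power at 0.4 | Rejection under the null |
|---|---|---|
| Change score, never adjusted | 78.8% | 5.0% |
| Adjust only if imbalanced | 79.7% | 4.3% |
| Always adjust | 88.6% | 5.0% |

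In this setting the conditional rule recovers about 1 of the roughly 10 percentage points available, and it does not inflate type I error.

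**Step 5: how easily the trigger fires.** If 10 independent characteristics were screened at p < 0.05, at least one would differ by chance in 1 − 0.95^10 = 40% of trials. For 20 it is 64%. The threshold is my assumption, because the article gives none.

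**The case against.** **The gain may be small.** The familiar (1 + rho)/2 needs equal SDs at baseline and week 24. Eligibility requires a minimum symptom severity (Table 2), so a narrower spread at baseline is plausible, though not documented. This stands: the gain in equivalent participants runs from about 0 to 93 over the range above and cannot be quoted as one figure.

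**The power figures are not for the planned test.** They are for a single contrast without the instructor effect, whereas the plan looks at contrasts only after a significant five-group test. Baseline adjustment need not reduce between-instructor variance. This also stands, so the figures show direction and rough scale only.

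**The change score is valid.** Under randomization it is unbiased on average, and the stated power was set on change and reproduces. The design is not underpowered because of this choice.

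**The rule may describe a supplementary analysis.** The primary model is named in the sentence before it, so the adjusted regression could be an addition rather than a replacement. The text allows both readings. Under the supplementary reading the primary model is not data-dependent, but it still omits baseline FIQR.

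**The article is condensed.** A threshold and covariate list could sit in a fuller document. That answers a complaint about missing detail. It does not answer the point that the rule, as stated, selects covariates on observed imbalance.

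**Stronger readings to avoid.** A reader might infer an inflated false-positive rate, but the simulated rule rejected 4.3% under the null. A reader might also cite the over-correction of the change score: in null trials with baseline imbalance at p < 0.05, it rejected 19% of the time at rho = 0.5. That figure belongs to an analysis that never adjusts. The plan's rule would adjust for a substantial FIQR difference, so it does not describe the plan.

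**Conclusion.** The point holds as one of precision and prespecification, not of bias or error rate. The stated rule brings in covariates on an undefined, data-dependent trigger and leaves baseline FIQR out of the primary model by default.

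Always adjusting for baseline FIQR is, in large samples, at least as precise as the change score whatever the correlation and SDs. With an assumed correlation of 0.4 to 0.7 and equal SDs, the variance falls by 15% to 30%, and single-contrast power rises from about 79% to 85–91%. With the baseline SD at 0.8 of the week-24 SD, the variance falls by only 2% to 16%. At an SD ratio of 0.7 and a correlation of 0.7 there is no gain. All of these figures rest on assumed correlations and SD ratios, on reading 0.4 as SDs of change, and on leaving out the instructor effect and the overall test.

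The change is worth making because it removes discretion at almost no cost, even where the gain in precision turns out small.

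**What to change.** - Prespecify baseline FIQR as a fixed covariate in the primary mixed model and in the models for FIQR change at 12 and 52 weeks.
- For secondary outcomes that have a baseline value, use that value as the covariate. This cannot apply throughout: in Table 1 the outcome expectations scale for the assigned intervention has no baseline measurement, and the personality inventory is given only once.
- Name any further covariates in advance, chosen for expected prognostic value.
- Delete the imbalance-triggered rule, or keep it only as a labelled sensitivity analysis with its threshold and candidate variables defined. Either way, state that it does not replace the primary model.

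The cost is a few lines of analysis text and one degree of freedom per model. No new data, visits or participants are needed.
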